**4.15.3 Muscle Strength**

Muscle strength will be evaluated at 8 and 12 weeks by progressive dumbbell lifting (RLM, Maringá, Paraná, Brazil) with elbow flexion in both arms. Progressive lifting will begin with 500 grams in the unaffected arm and increase to the maximum weight the participant can sustain, not exceeding 5 kg (Barbosa et al., 2008). Each dumbbell weight will be lifted only once per arm. Results will be recorded on the corresponding clinical forms for each experimental period (**Appendices 7 and 8**).

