**3.2. Secondary Objectives**

The secondary outcomes will evaluate the effects of PBM applied after proximal humeral fractures treated with ORIF, stabilized with fixed-angle plates, and managed with physiotherapy on:

- Shoulder range of motion (ROM), assessed over time and compared with the unaffected limb.
- Muscle strength, measured over time and compared with the unaffected limb.
- Intensity of spontaneous pain and pain during limb function.
- Occurrence of nighttime pain.
- Pressure pain at the fracture site.
- Analgesic consumption.
- Fracture consolidation.
- Quality of life.
- Incidence of adverse events.
- Direct and indirect costs associated with the procedures performed during the study period, for subsequent cost-effectiveness analysis of the intervention.

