**Inclusion Criteria:**

- Participants aged 18 to 65 years of both genders, with PHF classified as:
  - Neer group III
  - Neer group IV
  - Neer group V
  - AO/OTA subgroups A2 and A3
  - AO/OTA group B
  - AO/OTA group C (only in patients younger than 55 years).

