**Stage 1: First 3 weeks, starting 24 hours after surgery**

- Immobilization with a sling for the operated limb without weight-bearing.
- Initiation of pendulum exercises.
- Assisted passive movements.
- Avoid external rotation during the first 6 weeks.

**Stage 2: Third to ninth week, provided there are no abnormalities in consolidation or secondary displacement of fragments**

- Assisted active exercises, including flexion and abduction of the shoulder joint.
- Careful active exercises with limb abduction until pain occurs, with no weight-bearing in the first 6 weeks. Gradual weight addition will follow.

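### The 5 kg limit on the strength test conflicts with the planned comparison with the unaffected limb: the side-to-side deficit is understated wherever that limb can lift more (minor, one secondary outcome)

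*Protocol*

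**What the plan says.** Protocol section 3.2 lists among the secondary objectives "Muscle strength, measured over time and compared with the unaffected limb". Section 4.15.3 sets the test: "Muscle strength will be evaluated at 8 and 12 weeks", "by progressive dumbbell lifting (RLM, Maringá, Paraná, Brazil) with elbow flexion in both arms". On the load it says "Progressive lifting will begin with 500 grams in the unaffected arm", and that it will then "increase to the maximum weight the participant can sustain, not exceeding 5 kg".

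The sentence that sets the limit names the unaffected arm, so the reference limb is certainly covered. With both arms tested the same way, the natural reading is that the limit covers both. A literature citation is the only support given for it.

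The section does not say how a participant stopped at 5 kg is told apart from one whose true maximum is 5 kg. The protocol gives no expected load, standard deviation or share of arms at the limit, for either limb.

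**The concern.** The comparison needs the unaffected limb's maximum. The test does not measure that maximum when it lies above 5 kg; it records 5 kg instead. A comparison of recorded values then shows a smaller deficit than exists, or none. This is a rule for collecting data, so no later analysis can recover the missing values.

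Two conclusions are at risk. One is that the operated arm has caught up with the other. The other is that PBM makes no difference to strength. Either could come from the limit rather than from the participants. The stake is confined to one of ten secondary objectives.

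**Working it through.** **Plan's own figure.** There is none for strength. The sample size of 42 was set for QuickDASH and does not bear on this point.

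**Without any outside figure.** Let U be the true maximum of the unaffected arm and A that of the operated arm. The recorded values are min(U, 5) and min(A, 5), so

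recorded deficit = min(U, 5) − min(A, 5).

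If U > 5 and A < U, this is below U − A. Illustrations:

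- U = 8, A = 4: true deficit 4 kg, recorded 5 − 4 = 1 kg.
- U = 10, A = 6: true deficit 4 kg, recorded 5 − 5 = 0 kg.

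The group contrast behaves differently. Take U = 10 in both groups and a true PBM gain of 1.5 kg (15 points on the ratio A/U):

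- Operated arms 3 v 4.5 kg: the kg difference stays 1.5. The ratio goes from 0.30 v 0.45 to 3/5 v 4.5/5 = 0.60 v 0.90, so 15 points become 30.
- Operated arms 6 v 7.5 kg: both are recorded as 5, so the kg and ratio differences are both zero.

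Capping the reference arm therefore lowers the deficit in both groups alike. The kg contrast shrinks only as operated arms reach 5 kg, and the ratio contrast can move either way.

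**Size, under assumptions.** None of these inputs is in the protocol. Simulation with 400,000 draws per group: U normal with the mean and SD shown; control ratio 0.3, 0.5, 0.7 or 0.9 (SD 0.15); PBM adds 0.10 to the ratio; recorded value = min(true, 5). The last three columns give results at the four ratios in that order.

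| Mean (SD) of U, kg | U at limit | Control operated arms at limit | Recorded / true control deficit | PBM effect on kg deficit retained |
|---|---|---|---|---|
| 4 (1.5) | 25% | 0, 1, 5, 17% | 92, 89, 84, 82% | 100, 98, 89, 71% |
| 6 (2) | 69% | 1, 8, 30, 56% | 67, 56, 43, 36% | 98, 82, 54, 28% |
| 8 (3) | 84% | 6, 28, 57, 76% | 43, 29, 18, 14% | 84, 54, 25, 11% |
| 12 (4) | 96% | 24, 61, 85, 93% | 21, 9, 4, 3% | 58, 23, 6, 2% |

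Example: mean 8 kg, ratio 0.5, true control deficit 4.00 kg, recorded 1.17 kg; 1.17/4.00 = 29%.

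The deficit is understated in every row. More than half of the kg effect is lost only where about 55% or more of the control operated arms are at the limit.

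With control ratios of 0.3 to 0.7 and a PBM gain of 0.15, the recorded control deficit is about 5% to 92% of the true one, and about 7% to 97% of the kg difference is retained. A rerun put the ends of these ranges within about three points of those figures, depending on whether loads are rounded down to 0.5 kg steps.

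**Ratio scale (PBM gain 0.15, 0.5 kg steps).** At 0.60 v 0.75, the true difference of about 15 points is recorded as 14.0, 10.3, 6.7 and 4.6 at means of 6, 8, 10 and 12 kg. At 0.30 v 0.45 and mean 8 kg, 14.8 points are recorded as 20.5. Over means of 4, 5, 6, 8, 10 and 12 kg and control ratios of 0.3, 0.4, 0.5 and 0.6, the recorded difference exceeded the true one in 14 of 24 combinations.

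**The case against.** Much of the opposing case stands, and it limits the point.

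- A reader might infer that most uninjured adult arms reach 5 kg. The protocol admits "Participants aged 18 to 65 years of both genders" but gives no strength values, and the source cited for the method is not available here. This can only be an assumption with a range.
- A reader might infer that the limit hides most of a PBM effect. That requires many operated arms at 5 kg, on which the protocol is silent. Its rehabilitation plan (section 4.11, Stage 2), "with no weight-bearing in the first 6 weeks. Gradual weight addition will follow", points the other way, at least at week 8. Losing most of the effect is one end of a wide range, and on the ratio scale the contrast is often enlarged. Capping also reduces variance: with 18 per group (21 × 0.85 = 17.85) and the 0.10 gain, power on the kg deficit rises from 0.20 to 0.38 at mean 6 kg and ratio 0.3, and falls from 0.39 to 0.09 at mean 12 kg and ratio 0.7.
- A reader might object that elbow flexion does not measure shoulder strength. The protocol claims only muscle strength and names the movement openly, so there is no misstatement to correct.
- The protocol does not commit to a ratio, and the choice of a censored-data model is commonly left to a statistical analysis plan. Its absence is not a fault.
- The load limit may have a clinical reason that is not visible here, so raising or removing it should not be prescribed.

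What the objection does not remove is the mismatch itself. The protocol fixes both the limit and the comparison, and no analysis plan can restore a reference maximum that was not measured.

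**Conclusion.** The point holds as a cheap improvement to one secondary outcome. That the deficit is understated when the unaffected arm exceeds 5 kg and the operated arm is weaker, and recorded as zero when both arms reach 5 kg, follows from the test rule alone. How often and by how much depends on strengths the protocol does not give; the ranges above are conditional on the assumed means and ratios. For the PBM-control contrast, the documents support only that the kg difference is reduced to the extent that operated arms reach 5 kg, and that a ratio of capped loads is unreliable in either direction. They do not support a claim that a PBM effect will be hidden.

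**What to change.** 1. In section 4.15.3, record a lift stopped at the limit as '5 kg or more', distinct from a measured maximum of 5 kg.
2. Make the between-group strength outcome the operated-arm load at 8 and 12 weeks, with values at 5 kg treated as right-censored (for example a Tobit model).
3. Report the number of participants at the limit by limb, group and visit.
4. State that no conclusion of 'no deficit' or 'no PBM effect' will be drawn from a comparison of capped values.
5. The investigators should reconcile the load limit in section 4.15.3 with the comparison in section 3.2. No particular limit is proposed here.

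The cost is some protocol wording, one extra code on the week 8 and week 12 forms, and a slightly more complex analysis of one secondary outcome. If most operated arms turn out to be at the limit, the censored analysis will carry little information; the counts in step 3 will show this.

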**4.15.4 Pain Assessment**

The intensity of spontaneous pain and pain during the function of the injured limb will be evaluated using the visual analog scale (VAS) for pain (Jensen et al., 1986). The chosen scale, represented in Figure consists of a 10 cm numbered line featuring facial expression illustrations, a color gradient, and indications of mild, moderate, and severe intensities to facilitate understanding (Thong et al., 2018).

[figure not shown]

**Figure 11.** Visual analog pain scale.

Pressure pain at the fracture site (**Figure**) will be assessed using a digital algometer (MED DOR, Governador Valadares, MG, Brazil).

[figure not shown]

**Figure 12.** Digital algometer in position for measuring pressure pain.

Results regarding spontaneous pain, pain during function (flexion and abduction), and pressure pain measured using the algometer will be collected 1 day after surgery and subsequently at 1, 2, 4, 8, and 12 weeks. These results will be recorded in the respective clinical forms (Appendices 3 to 8) for each experimental period.

Nighttime pain occurrence will be assessed during daily PBM usage monitoring and recorded in the participant's daily control form (Appendix 2).

**4.15.5 Analgesic Consumption**

The type and dosage of analgesics consumed will be assessed during daily PBM usage monitoring and recorded in the participant's daily control form (**Appendix 2**).

**4.15.6 Quality of Life**

Quality of life will be evaluated using the SF-6 instrument from 2002 (Appendix 3) in its version adapted for use in Brazil (Campolina et al., 2011). Assessments will take place at 1, 2, 4, 8, and 12 weeks, with results recorded in the respective clinical forms (Appendices 3 to 8) for each experimental period.

In the most recent Brazilian version of SF-6 (2002), as in the original, six items are included:

- Functional capacity (items 1, 2, and 10)
- Global limitation (item 3 for physical aspects and item 2 for emotional aspects)
- Social aspects (item 2)
- Pain (all items)
- Mental health (item 1)
- Vitality (item 2) (Campolina et al., 2011).

**4.15.7 Adverse Events**

The occurrence of adverse events will be assessed during daily PBM usage monitoring and recorded in the participant's daily control **form (Appendix 2).**

**4.15.8 Fracture Consolidation**

Shoulder X-rays (anteroposterior, scapular profile, and axillary views) will be taken at 4, 8, and 12 weeks to evaluate bone consolidation. Consolidation will be defined by the presence of a callus in three out of four bone cortices uniting the main fracture fragments, compared with the immediate postoperative X-ray (Gracitelli, 2015).

**4.15.9 Cost Analysis**

The costs will be calculated from the perspective of the Unified Health System (SUS) as the service purchaser. Direct costs of the procedures performed during the study period will be considered, including material costs, professional fees, hospital expenses, and productivity loss due to work absence.

Cost references in Brazilian currency (Real) will be sourced from the ComprasNet, SIGTAP, and Price Database of the Ministry of Health. The final cost-effectiveness and incremental cost analysis will follow the guidelines of the Methodological Guidelines: Economic Evaluation Studies of Health Technologies and the National Policy for Health Technology Management (BRASIL, 2010).

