**Table 3: Treatment Costs**

| **Costs** | **Estimated Value (R$)** |
| --- | --- |
| Daily hospital stay in public network ward |  |
| Orthopedic care with provisional immobilization |  |
| Emergency room fee |  |
| Cast room fees |  |
| Antiseptic solution |  |
| Suture threads |  |
| Surgical compress |  |
| Surgical arch/intensifier usage |  |
| Pneumatic drill for surgery usage |  |
| Aspirator usage |  |
| Oximeter usage |  |
| Multifunction monitor (per hour) |  |
| Anesthesia machine usage |  |
| Dipyrone Monohydrate 2 ml ampoule |  |
| Tramadol Hydrochloride 100 mg ampoule |  |
| Enoxaparin 40 mg ampoule |  |
| Omeprazole 40 mg ampoule |  |
| Ondansetron 8 mg ampoule |  |
| Cefazolin Sodium 1 g ampoule |  |
| Morphine Sulfate 2 ml ampoule |  |
| Imaging exams (CT and X-rays) |  |
| Sterile gauze 13 threads |  |
| Cremer elastic bandage 10 cm x 1.8 m |  |
| Hospital dressing change |  |
| Daily cost of absent worker (indirect cost) |  |
| Disability aid (estimated, indirect cost) |  |
| Physiotherapy session |  |
| PBM device |  |
| **TOTAL** |  |

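### The cost analysis is declared from the public purchaser's perspective but includes lost work and disability aid, so an increment labelled as the purchaser's would contain items outside that perspective

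*Protocol*

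**What the plan says.** Three places in the protocol bear on this point.

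- **Section 4.15.9 (Cost Analysis)** sets the perspective: "The costs will be calculated from the perspective of the Unified Health System (SUS) as the service purchaser". The next sentence names the cost category, "Direct costs of the procedures performed during the study period will be considered", and completes the list with "including material costs, professional fees, hospital expenses, and productivity loss due to work absence". The section then says of the economic result: "The final cost-effectiveness and incremental cost analysis will follow the guidelines", referring to national methodological guidance. On prices it says: "Cost references in Brazilian currency (Real) will be sourced from the ComprasNet, SIGTAP, and Price Database of the Ministry of Health".
- **Table 3 (Treatment Costs)** has one line "Daily cost of absent worker (indirect cost)" and another "Disability aid (estimated, indirect cost)". Both stand in the same column as the hospital, drug, imaging, physiotherapy and device lines, above one total row. All value cells are empty.
- **Section 3.2 (Secondary Objectives)** lists as its last item: "Direct and indirect costs associated with the procedures performed during the study period, for subsequent cost-effectiveness analysis of the intervention".

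**The concern.** The perspective of an economic evaluation decides which costs count. A purchaser of health services pays for materials, professional time, hospital care and devices. It does not buy the working days that a patient loses, so lost work belongs to a wider, usually societal, perspective. Section 4.15.9 declares the narrow perspective and includes a wide-perspective item in the next sentence, under the name of a direct cost. Table 3 gives the same kind of item the opposite label and adds disability aid, which section 4.15.9 does not mention.

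What is at stake is the meaning of the incremental cost. A reader who sees a result described as the SUS purchaser's will take it as the change in what SUS pays. If lost work and aid are inside it, it is a different quantity, and a between-arm difference in time off work would appear as a saving or a cost to the health system.

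**Working it through.** The protocol gives no cost figure to reproduce. The check sets the three places side by side and then uses algebra.

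**Side by side**

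| Question | Section 3.2 | Section 4.15.9 | Table 3 |
| --- | --- | --- | --- |
| Perspective | not stated | SUS as purchaser | not stated |
| Cost categories | direct and indirect | direct | both, above one total |
| Lost work | not named | included, as direct | included, as indirect |
| Disability aid | not named | not named | included, as indirect |

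Two contradictions follow. Lost work is direct in section 4.15.9 and indirect in Table 3. The analysis covers direct costs only in section 4.15.9, but direct and indirect costs in section 3.2 and Table 3. In addition, the cost items go beyond the one perspective declared, and no second perspective is declared to hold them.

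**What this does to the increment**

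For each cost, let Δ be the mean in the PBM group minus the mean in the control group. Write H for health-care costs paid by SUS, A for the cost of work absence, D for disability aid and E for the effect measure.

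- Purchaser's increment: ΔH.
- Increment with the cost list of section 4.15.9: ΔH + ΔA.
- Increment with all lines of Table 3: ΔH + ΔA + ΔD.
- Departure of the Table 3 version from the purchaser's: (ΔH + ΔA + ΔD) − ΔH = ΔA + ΔD.
- If a ratio is formed, it departs by (ΔA + ΔD)/ΔE.

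The departure is zero only if the arms do not differ on the net sum of the two items. If the groups differ by k days of absence and a day is costed at d, then ΔA = k × d. The value of d is blank in Table 3, the protocol anticipates no k, and the aid value is blank as well. No amount and no sign can be given.

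**Why the two lines are not negligible by construction**

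Only costs that differ between arms enter an increment. Under section 4.7 the envelope is opened 24 hours after surgery, so emergency, theatre and anaesthesia costs arise before allocation and should balance in expectation. Physiotherapy is standardised for all participants (section 4.11), and radiographs follow one schedule for everyone (section 4.15.8). What can still differ is the PBM device, care after allocation (further hospital days, analgesia, dressings) and the two indirect lines. Those two are a small part of the table's rows but may be a larger part of the increment. How much larger cannot be said.

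**The case against.** The strongest reply has four parts.

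1. **Indirect costs are openly planned.** Section 3.2 names them, so nothing has been slipped in. This stands, and it means the fault is a mismatch between the declared perspective and the items, not an undisclosed addition. It also means that redeclaring the perspective as societal would be another way to reconcile the text. It does not turn lost work into a purchaser's cost or into a direct one.
2. **The total in Table 3 is not shown to be the numerator of any ratio.** The table has no quantities and no columns by group, and many lines are unit prices, so it may be only a price inventory. This is fair. However, section 4.15.9 puts lost work into the costs to be considered without any help from the table, so the contradiction does not depend on how the total is used.
3. **The national guidance, or an analysis plan not at hand, may separate the perspectives.** That is possible, and missing detail would be no finding. Here the protocol itself fixes both the perspective and the items, and the two disagree.
4. **The effect is unquantified and concerns a secondary objective.** This stands in full.

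Three stronger readings are tempting, and the protocol supports none of them. A reader might infer that the plan misreports a stated cost-effectiveness ratio, but it states no ratio, formula or effect measure for one. A reader might infer that work absence would decide the sign of the result, but all values are blank and care after allocation can differ too. A reader might infer that lost work and disability aid are certainly counted twice. That holds only if the aid replaces the same loss, and the protocol does not say what the aid covers or who funds it.

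**Conclusion.** The inconsistency is real and can be read directly from sections 3.2 and 4.15.9 and Table 3. Followed as written, the plan would yield an incremental cost called the SUS purchaser's that contains items outside that perspective. It would differ from the purchaser's increment by ΔA + ΔD, of unknown size and direction. The conclusion rests on one premise, the ordinary meaning of a service purchaser's perspective, under which lost working days are not a purchased service. Treating disability aid as outside the perspective rests on the table's own label of indirect cost and on the same meaning.

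The consequence is confined to the economic secondary objective. The Quick-DASH comparison and the sample size are untouched. It should be corrected before costs are compared between groups, so that the choice of items is not made with the results in view.

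**What to change.** Reconcile sections 3.2 and 4.15.9 and Table 3 as follows.

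- Report the SUS-perspective result with health-care costs only.
- Report a separate analysis, labelled societal, that adds the indirect costs. Section 3.2 then keeps its direct and indirect costs, each with a stated place.
- In section 4.15.9, take productivity loss out of the list of direct costs, and call it indirect wherever it appears.
- Split Table 3 into a direct and an indirect subtotal.
- State whether disability aid compensates the same absence as the absent-worker cost. If it does, do not sum the two.

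The cost is a change of wording and of table layout. Nothing planned is dropped, and no further data are needed beyond what the listed cost items already require.

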**Table 3: Treatment Costs**

| **Costs** | **Estimated Value (R$)** |
| --- | --- |
| Daily hospital stay in public network ward |  |
| Orthopedic care with provisional immobilization |  |
| Emergency room fee |  |
| Cast room fees |  |
| Antiseptic solution |  |
| Suture threads |  |
| Surgical compress |  |
| Surgical arch/intensifier usage |  |
| Pneumatic drill for surgery usage |  |
| Aspirator usage |  |
| Oximeter usage |  |
| Multifunction monitor (per hour) |  |
| Anesthesia machine usage |  |
| Dipyrone Monohydrate 2 ml ampoule |  |
| Tramadol Hydrochloride 100 mg ampoule |  |
| Enoxaparin 40 mg ampoule |  |
| Omeprazole 40 mg ampoule |  |
| Ondansetron 8 mg ampoule |  |
| Cefazolin Sodium 1 g ampoule |  |
| Morphine Sulfate 2 ml ampoule |  |
| Imaging exams (CT and X-rays) |  |
| Sterile gauze 13 threads |  |
| Cremer elastic bandage 10 cm x 1.8 m |  |
| Hospital dressing change |  |
| Daily cost of absent worker (indirect cost) |  |
| Disability aid (estimated, indirect cost) |  |
| Physiotherapy session |  |
| PBM device |  |
| **TOTAL** |  |

